### Interventions

#### Arm 1: Radiotherapy ± chemotherapy (RCT)

Volumetric Modulated Arc Therapy (VMAT) with simultaneous Integrated Boost (SIB) will be used for all patients in this study.

For all cT1-T2N0 tumors, patients will be treated with moderately accelerated radiotherapy alone. Primary Gross Tumor Volume (GTVp) will be delineated according to the clinical examination and the available imaging. A 10 and a 5 mm margins (adapted to anatomical barriers) will be added to generate the Primary Clinical Target Volumes (CTVp) treated at prophylactic and radical (or therapeutic) doses, respectively (according to the current guidelines [49–51]):The therapeutic CTVp includes the tumor area and the high-risk location. It will be irradiated up to a total dose of 69 Gy in 30 fractions (2,3 Gy/fraction, 5 fractions a week during 6 weeks) or 70 Gy in 35 fractions (2,0 Gy/fraction, 6 fractions a week during 6 weeks).The prophylactic CTVp includes the elective mucosa. It will be irradiated up to a total dose of 54 Gy in 30 fractions (1,8 Gy/fraction, 5 fractions a week during 6 weeks) or 54,25 Gy in 35 fractions (1,55 Gy/fraction, 6 fractions a week during 6 weeks).

Elective CTVn must be selected and delineated according to the international recommendations and treated at prophylactic dose [50, 52].

All CTVs will be expanded by an isotropic 3–5 mm margin to generate the related Planning Target Volume (PTV). Margin may be cropped at level of skin for correct optimization and avoiding skin overdosage.

For all cT1-T2 N1 tumors, patients will be treated with concurrent radio-chemotherapy [49–51]. Selected patients with a “small” positive node (I.E., centimetric) or having an absolute contra-indication to chemotherapy may be treated with radiotherapy alone.

In the case of concomitant chemotherapy, the selection, delineation and prescription will follow the same principles as stated above, except that.Nodal Gross Tumor Volume (GTVn) will be delineated according to the clinical examination and available imaging. A 5 mm margin adapted to anatomical barriers will be added to generate the nodal Clinical Target Volume treated (CTVn), to be treated at therapeutic dose.Only normo-fractionated schedule may be used but may be accelerated at the discretion of the center by use of 6 fractions a week.The standard chemotherapy regimen is the Cisplatin 100 mg/m^2^ on days 1 – 22 and 43 (5 fractions a week) or on days 1 and 22 (6 fractions a week). In case of contra-indication to cisplatin, alternatively, carboplatin-5FU may be administered on weeks 1, 4 and 7 (5 fractions a week) or on weeks 1 and 4 (6 fractions a week). Weekly schedules or cetuximab or any other investigational or non-investigational radio-sensitizing drugs are not allowed.

#### Radiotherapy quality assurance

Before authorization and inclusion to participate in this study, each center must perform a Dummy Run. This consists to a delineation and planning exercise according to the protocol in a provided patient case. This will be reviewed by our radiotherapy expertise committee.

After inclusion, the three first patients must be submitted for central review of the planned treatment and delineation before radiotherapy starting. After that, randomly selected cases will be reviewed on request of the radiotherapy expertise committee.

#### Arm 2 and 3: Trans-oral Surgeries

Trans-oral surgeries can be performed by TLM or by TORS. The choice of the technique will be made during the local MTB and depending the local expertise.

Surgery must be performed within the 4 weeks after pathological confirmation of SSCC with primary tumor biopsy.

A good surgical field exposure is mandatory. The use of an appropriate mouth gag is recommended. The exposure will be evaluated before the main surgery during a rigid panendoscopy. In case of doubt, the mouth gag needs to be tested during this procedure.1/ Trans-oral laser microsurgery (TLM).

A microscope with a CO_2_ laser will be used for the resection and hemostasis.

The best adapted laryngoscope to the patient anatomy should be used for an adequate exposition.

The hemostasis can be performed by a monopolar of the use of clips.

During the procedure, the superior laryngeal arteries should be ligated or clipped.2/ Trans-oral robotic surgery (TORS).

TORS will be carried out using the Da Vinci Surgical robot (Intuitive Surgical, CA, USA). Surgeons on the main console and at the bedside should have adequate training and an experience of minimum 20 cases. The spatula cautery will be used to remove the tumor and perform hemostasis at the same time. The hemostasis and bleeding prevention should be made with the bipolar or using clips. During the procedure, the superior laryngeal arteries should be ligated or clipped.3/ Handling of Surgical Margins.

The surgeon should try to achieve a minimum of 1 cm gross visual margins with > 3 mm microscopic margins. The resection needs to completely remove the tumor and *en-bloc* resection is preferred. The resection will be performed according the European Laryngological Society classification of endoscopic supraglottic laryngectomy [53]. In the TLM, the piecemeal resection is sometimes necessary to obtain adequate deep section margins. In this case, all the pieces of the specimen must be oriented and pinned carefully on the cork-board. The help of a schematic anatomical view is mandatory.

During the surgery, circumferential margins will be evaluated by frozen section peroperative analysis. These margins will be oriented as followed: superior, inferior, lateral, medial and deep. If needed, further resections will be performed until negative margins are obtain. The resected specimen should be oriented with the help of a schematic view on the cork-board.

Definition of the margins [54, 55]:Clear margins (R0): when margins are > 3 mm on the final pathology specimenClose margins: when they are between 1 and 3 mm.Positive margins (R1) when they are < 1 mm

If a positive (R1) or close margin is found on the final pathology analysis, an attempt to clear the margin may be performed within 2 weeks after the original resection in order to obtain an R0-status with the help of a new trans-oral resection in the closed/positive margins area. If clear margins cannot be obtained, postoperative radiotherapy ± chemotherapy will be administered (see below).4/ Neck dissection.

In both surgical arms (Arms 2 and 3), all patients will undergo standard elective neck dissections (END) for the lymph node areas at risk on the same day of the main surgery, or differed for a maximum of 2 weeks, at the discretion of the surgeon [25]. In case of a cN0 neck, END will be limited to the levels II – III and IV. In case of a cN1 neck, and when the levels I or V are involved, the neck dissection will include these levels.

About the side:- any lesion more than 5 mm away from the midline, a unilateral same side END is sufficient.- for lesions closer or equal than 5 mm to the midline, a bilateral END will be done.The END should be oriented or separately partitioned in order to identify the level of the lymph involved on the final pathology [56–58].

5/ Reconstruction.

Healing of the defect is generally by secondary intention. In some rare cases, a primary closure is performed by trans-oral approach. In these T1 and T2 cases, the reconstruction with flaps can generally be avoided [25].

In case of complications likes communication between the neck dissection site and the tumor resection bed or pharyngo-cutaneous fistula, a reconstruction with flaps can be used. The choice of the subtype of flaps (pectoralis; forearm free-flap, anterolateral thigh free-flap, etc.) is left at the discretion of the surgeon or the plastic surgeon and depends on his expertise.6/ Post-operative care.

Extubation: can be performed the same day or the day after the surgery, at the surgeons’ and anesthetists’ discretion [59]. A tracheostomy should typically not be required but can be performed in case of bleeding or edema risk. The need for a protective tracheostomy is judged by the surgeons and is not considered as a complication if it’s performed on the same day as the surgery. The use of a tracheostomy should also be collected.

The use of nasogastric tube or gastrostomy: is necessary at the end of the procedure. The choice of the type of interventions is left at the discretion of the surgeon and depends of the patient swallowing capabilities before the surgery. The use of nasogastric tube is preferred. The number of days and the type of support should be collected in the study [60].

In case of bleeding after the surgery: the management needs to be optimal and the safest for the patient [61]. If a surgical revision must be performed, the trans-oral approach should be preferred. The hemostasis can be done by vessels clipping, bipolar or monopolar-suction device, depending of the experience of the surgeon. If it is not sufficient, an external neck ligation of the superior laryngeal artery or the superior thyroid artery can be needed. A preventive tracheostomy can be achieved to protect the upper airways. The need of a transfusion can also be considered especially for patients with a cardiac problem history.

#### Therapy response summary (Fig. 2, Trial design)

For the Radiotherapy arm (Arm 1), the therapy response will be evaluated by the same modality as for staging (CT, MRI or PET-CT) 12–16 weeks after treatment, depending on local institutional standards. All patients must be discussed at the MTB with this imaging and clinical evaluation.In case of negative imaging, the patient will start the follow-up period of 2 years.In case of positive imaging, a panendoscopy with biopsy should be performed to confirm the residual/recurrence disease. Salvage surgery is recommended for residual or recurrent disease. For patients with residual nodes > 1 cm in size (smallest diameter), an ipsilateral neck dissection will be done. For patient with local residual or recurrent disease (at any time subsequent to radiation treatment), surgical salvage will be offered if feasible. The salvage surgery will be done by open (Total Laryngectomy) or transoral approach at the discretion of the treating surgeon and depending of the clinical situation.

For the surgical arms (Arms 2 and 3), all patients must be discussed in the MTB with the post-operative histological results. All volumes are drawn based on pre-op imaging.

Post-operative adjuvant radiotherapy alone will be performed in the presence of adverse pathological factors [32]:(a) close margins (1-3 mm);(b) peri-neural infiltration or lympho-vascular invasion.(c) pT3 disease.(d) 1 invaded lymph node > 3 cm (pN2a) or more than 2 invaded lymph nodes per side of the neck (pN2b).

The therapeutic CTV will consist of the primary tumor bed expanded in function of the quality of the surgical margins, and the eventual positive nodal levels. The elective CTV will be selected according to the international guidelines [62]. All CTVs will be expanded by an isotropic 3–5 mm margin to generate the related Planning Target Volume (PTV).

Therapeutic/elective doses will be prescribed to the respective PTV’s at 60/54 Gy in 30 fractions of 2/1,8 Gy and planned with SIB-IMRT.

Post-operative adjuvant chemo-radiation will be performed in case of [32].positive surgical margins in the definitive histology (< 1 mm) and no surgical revision possible;extracapsular extension in node(s).

Delineation of CTVs and PTVs will follow the same rules. Therapeutic/elective doses will be prescribed to the respective PTVs at 66/56,1 Gy in 33 fractions of 2/1,7 Gy and planned with SIB-IMRT. Concomitant radio-sensitizing chemotherapy with 3-weekly Cisplatin or Carboplatin-5FU will be prescribed following the same rules as for definitive-radiation.

In both cases, every reasonable effort should be made to start the post-operative (chemo)radiation within the 6 weeks after surgery.

In case of recurrence or secondary primaries, a new panendoscopy with biopsy must be performed and the results should be discussed at the MTB. In case of a very small recurrence of secondary primary, a new trans-oral procedure can be performed. In case of a bigger tumor, salvage radiotherapy should be preferred. In case of contra-indication to radiotherapy (e.g., previous radiation on the neck), a total laryngectomy or total pharyngo-laryngectomy is required.

## Statistical analysis

The primary outcome is the total MDADI scores at 12 months between the 3 arms. Assuming that the MDADI total score is normally distributed with a standard deviation of 12 points and considering a minimal clinical difference of 10 points [63], a sample size of 30 patients per arm with a confidence of 95% and a power of 90% is sufficient to detect a clinically significant difference [64–66]. Assuming a 20% of patient’s dropout, we need to recruit 36 patients per arm (total 108).

*The baseline characteristics* of the patients in the 3 arms will be described, including demographics and tumors measures at imaging, using descriptive statistics.

Differences will be assessed with a Tukey Test for K means or similar, and Chi-square tests for counts and frequencies as required.

Any difference in patient baseline heterogeneity between the arms will be assessed by the Charlson Comorbidity Index.

If a mismatch between the 3 groups in the baseline variables is discovered; a multivariate propensity scores analysis (PSA) will be undertaken to establish conditional randomness and comparability [67, 68].

*Survival rates* will be calculated from the date of MTB until the last available follow-up date or study cut-off at 2 years using the Kaplan–Meier method with differences compared using the log-rank test.

A Cox multivariate regression analysis will be used to determine baseline factors predictive of survival.

*MDADI, QLQ-C30 and H&N43 subscales* and single-item sub-scores will be summarized by means (standard deviation) and median for each trial arm and presented graphically using boxplots by trial arm and time period. The scores of the different scales will be compared between the 3 arms using mixed models for repeated measures.

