## Methods – design

We propose to carry out an observational non-randomized prospective clinical trial on patients diagnosed with an early SSCC where 3 subgroups are studied in parallel:Arm 1: Radiotherapy ± chemotherapy (RCT)Arm 2: Trans-oral Laser Microsurgery (TLM)Arm 3: Trans-Oral Robotic Surgery (TORS)

The inclusion will be multicentric and international. The treatment will be chosen by the local multidisciplinary tumor board (MTB) according to the primary cTNM-stage, the patient preferences and the local standard of care based on peer-reviewed international guidelines (Fig. 1, SPIRIT Flow Chart and Fig. 2, Trial Design). The guidelines to be followed are the National Comprehensive Cancer Network (NCCN) [31] or the European guidelines including the European Head and Neck Society (EHNS), the European Society of Medical Oncology (ESMO) and the European Society for RadioTherapy and Oncology (ESTRO) [32].

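### The 90% power figure fits one unadjusted two-group comparison, but the primary comparison has three arms; for a given 10-point pair with familywise control, power is about 76–80%

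*Protocol article*

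**What the plan says.** In the Statistical analysis section, "The primary outcome is the total MDADI scores at 12 months between the 3 arms". The design section describes a study "where 3 subgroups are studied in parallel": radiotherapy with or without chemotherapy, TLM and TORS. No arm is named as control and no pair is ranked above another.

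The sample size assumes a total score that is "normally distributed with a standard deviation of 12 points". The target effect is set by "considering a minimal clinical difference of 10 points". It concludes that "a sample size of 30 patients per arm with a confidence of 95% and a power of 90% is sufficient to detect" such an effect. "Assuming a 20% of patient’s dropout", recruitment is set at 36 per arm, 108 in total.

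The calculation does not say which test it is for, whether it is one- or two-sided, how the 10 points are spread over three means, or whether the 5% level covers one comparison or several. A Tukey test is named later in the section, directly after the sentence on baseline characteristics, so it is unclear whether it applies to the primary outcome. MDADI itself is to be compared across the three arms with mixed models for repeated measures. No multiplicity rule is attached to that comparison.

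**The concern.** A difference, an SD, a confidence level and a power are enough for a two-group calculation. A three-arm comparison also needs a test and either a pattern of means or a set of contrasts with an error rule. The stated inputs stop at the first list, while the primary outcome is of the second kind.

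The aim is a head-to-head comparison of three treatments, so readers will ask which pairs differ. If each pair is tested at 5%, the chance of at least one false claim exceeds 5%. If the family is controlled, the power for a given pair falls below the stated 90%. Either way the 90% does not describe that question. A null TORS versus TLM result, for example, could be taken as 90%-powered evidence against a 10-point gap when the true power was nearer 78%.

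**Working it through.** **Inputs from the Statistical analysis section:** difference δ = 10, SD σ = 12, 5% level, power 90%, 30 evaluable per arm, 36 recruited per arm, 20% dropout. Evaluable after dropout: 36 × 0.80 = 28.8 per arm.

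**Assumptions:** two-sided tests, equal arms, common SD, no gain from baseline adjustment.

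**1. Reproducing the plan's figure.** Two-group normal formula at an unadjusted 5%:

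n = 2(1.96 + 1.2816)² × 12² / 10² = 2 × 10.508 × 1.44 = 30.3 per arm.

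This matches the stated 30. At n = 30, power is 89.8% by the normal approximation and 88.8% by the exact two-sample t test (58 df). A one-sided test does not fit: it needs only 25 per arm.

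**2. A given 10-point pair, with control over three pairs.** The noncentrality is δ / (σ√(2/n)):
- n = 30: 10 / (12 × 0.2582) = 3.227
- n = 28.8: 10 / (12 × 0.2635) = 3.162

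Critical values use the pooled variance with 3n − 3 df. At n = 30 they are q(0.95; 3, 87)/√2 = 2.384 for Tukey and t(1 − 0.05/6; 87) = 2.441 for Bonferroni. Power is then taken from the noncentral t distribution.

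**3. Omnibus F test at 5%.** The noncentrality is λ = n Σ(μᵢ − μ̄)² / σ², with 2 and 3n − 3 df:
- Means 0, 5, 10: Σ = 25 + 0 + 25 = 50, so λ = 30 × 50 / 144 = 10.42 at n = 30 and 10.00 at 28.8.
- Means 0, 0, 10: Σ = 11.11 + 11.11 + 44.44 = 66.67, so λ = 13.89 and 13.33.

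**Results**

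| Reading | n = 30 | n = 28.8 |
|---|---|---|
| One pair, unadjusted two-sample t | 88.8% | 87.4% |
| Given pair, Tukey | 79.9% | 77.9% |
| Given pair, Bonferroni (pooled df) | 78.2% | 76.2% |
| Omnibus F, means 0/5/10 | 81.8% | 80.0% |
| Omnibus F, means 0/0/10 | 91.7% | 90.5% |

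**4. Error rate if all three pairs are tested unadjusted.** With all means equal, the chance of at least one rejection is about 12.1%. It is below the 14.3% of three independent tests, 1 − 0.95³, because the pairs share arms.

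**5. What 90% per controlled pair would need.** About 39 evaluable per arm with Tukey (90.2%) or 40 with Bonferroni on pooled df (90.1%).

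**The case against.** The strongest counter-argument is that the article may have meant a three-arm test all along. With one arm 10 points from two equal arms, an omnibus F test needs 29 per arm for 90% and still has 90.5% after dropout. That fits the wording of the primary outcome. The two-group formula gives 30.3, which strictly rounds up to 31, so it does not return exactly 30 either. The references cited for the calculation are not at hand.

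This much stands: a reader might infer that 30 per arm can come only from a two-sample test, or that the design delivers 80% or less whatever the analysis. The documents support neither. Nor does the article declare three pairwise contrasts as the confirmatory family; that is inferred from the head-to-head aim and the absence of a named pair.

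Two further objections have some weight. The Tukey sentence shows that multiple comparison was not wholly overlooked, though its place after the baseline paragraph leaves its scope open. If it does govern the primary outcome, the applicable power is 78–80%, not 90%. Secondly, a mixed model that uses baseline MDADI could gain precision. If the baseline to 12-month correlation were 0.3 to 0.5 (an assumption; the article gives none), Tukey power per pair would be about 82–89% at 28.8 per arm and 84–91% at 30. The fixed centre effect and any propensity adjustment also alter precision, in directions that cannot be computed from the text.

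It may also be said that contrasts and multiplicity rules belong in the analysis plan, which is not shown. That would answer a complaint about missing detail. Here the point is a stated power figure that the stated inputs support only for a question other than the likely one.

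The favourable omnibus reading does not rescue the claim. It rests on a test and a pattern of means that the article does not state, and a rejection would not say which arms differ. In that same pattern at 30 per arm, the simulated chance of detecting both true 10-point gaps is about 69% with Tukey and 82% unadjusted.

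**Conclusion.** The point holds in conditional form. The stated 30 per arm and 90% match a single unadjusted two-sided two-group comparison, while the primary comparison has three arms with no pair singled out. Of the readings in the table, only the omnibus test with one arm 10 points from two equal arms reaches 90%. For a given 10-point pair with familywise control, the shortfall from 90% is about 10 to 12 percentage points at 30 per arm and 12 to 14 at 28.8. For the omnibus test in the 0/5/10 pattern it is 8 and 10 points. For one unadjusted pair it is small, 1 to 3 points.

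These figures rest on the article's own difference, SD and dropout, equal arms, two-sided testing and no covariate gain.

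**What to change.** Name the primary test and the contrast or contrasts for 12-month MDADI, and restate the power that 108 enrolled patients give for that choice after 20% dropout. Two options need no extra patients:
- **All three pairs primary with Tukey control:** about 78% for a 10-point difference in a given pair.
- **One pair declared the sole primary contrast, the other two secondary:** about 87% for that pair.

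If the omnibus test is intended, say so, give the assumed pattern of means (80% for 0/5/10, 90.5% for 0/0/10), and say how pairs will be examined after a rejection. State whether the Tukey sentence covers the primary outcome or only the baseline comparisons. Report any expected gain from baseline adjustment separately, with the assumed correlation.

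The cost is a change of wording and a less favourable stated power. Keeping 90% for every controlled pair would instead need about 39–40 evaluable per arm, that is 39/0.80 = 48.75 to 40/0.80 = 50, so 49–50 recruited per arm against the planned 36.

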**Methods/design:**

We will conduct an original international multicentric prospective nonrandomized clinical trial to compare the efficacy between these treatments (Arm 1: Radiotherapy ± chemotherapy; Arm 2: TLM and Arm 3: TORS) with 4 classes of outcomes: quality of life (QoL), oncological outcomes, functional outcomes and economic resources. The population will include cT1-T2 /cN0-N1/M0 supraglottic squamous cell carcinoma. The primary outcome is a Clinical Dysphagia QoL evaluation assessed by the MD Anderson Dysphagia questionnaire. Secondary outcomes include others QoL evaluation, oncological and functional measures and cost parameters. The sample size needs to reach 36 patients per arm (total 108).

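### Recruiting 36 per arm does not leave the required 30 after 20% dropout: 28.8 are expected, and the matching figure is 38 (a minor arithmetic error)

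*Protocol article*

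**What the plan says.** The primary endpoint is the 12-month total MDADI score: "The primary outcome is the total MDADI scores at 12 months between the 3 arms". In the protocol article, the Statistical analysis section takes the score to be "normally distributed with a standard deviation of 12 points", sets the target by "considering a minimal clinical difference of 10 points", and concludes that "a sample size of 30 patients per arm with a confidence of 95% and a power of 90% is sufficient". It then assumes 20% dropout and states "we need to recruit 36 patients per arm (total 108" overall). The Methods/design paragraph of the abstract repeats the target: "The sample size needs to reach 36 patients per arm (total 108" in total).

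The article shows no inflation formula and describes no replacement of patients who drop out. It also does not name the test behind the 30 or say whether it is one- or two-sided.

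**The concern.** A dropout allowance should ensure that, when the assumed share of recruited patients is lost, the required number is still expected to remain. Here the required number is 30 and the assumed loss is 20%, but the recruited number leaves fewer than 30. The allowance appears to have been made by adding 20% to 30 rather than dividing 30 by the share retained.

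At stake is the accuracy of the sample-size statement for the primary endpoint: under the plan's own dropout assumption, the recruitment target does not deliver the size said to give 90% power.

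**Working it through.** **Inputs**, all from the Statistical analysis section: SD 12; difference 10; 95% confidence, so alpha 0.05; power 90%; 30 per arm before dropout; dropout 20%; 36 per arm and 108 in total recruited. Two assumptions are added because the text is silent: the test is two-sided, and it compares two arms.

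**1. Reproduce the 30.** The normal formula for two means is n = 2 (z₀.₉₇₅ + z₀.₉₀)² SD² / difference².

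- 2 × (1.96 + 1.2816)² × 144 / 100 = 30.26 per arm.
- A one-sided 5% test would need 25.

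The two-sided, two-arm calculation therefore accounts for the stated 30, apart from rounding.

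**2. Reproduce the 36.** 30 × (1 + 0.20) = 36, an exact match, and 3 × 36 = 108. Since the article gives no formula, multiplication by 1.2 is inferred from this match.

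**3. Apply the stated dropout to the stated recruitment.**

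- Expected to remain: 36 × (1 − 0.20) = 28.8 per arm, which is 1.2 short of 30.
- Dropout that 36 can absorb: 1 − 30/36 = 16.7%.

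**4. Recruitment that matches 30 and 20%.**

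- 30 / (1 − 0.20) = 37.5, rounded up to 38 per arm, and 3 × 38 = 114.
- Check: 38 × 0.80 = 30.4.
- Gap: 2 per arm, 6 overall.

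**5. Power for one unadjusted two-arm comparison.** The normal approximation is Φ(difference / (SD √(2/n)) − 1.96).

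- n = 30: 10 / (12 × √(2/30)) = 3.2275; Φ(3.2275 − 1.96) = 89.8%.
- n = 28.8: 10 / (12 × √(2/28.8)) = 3.1623; Φ(3.1623 − 1.96) = 88.5%.

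| Per arm | Normal approximation | t-test (noncentral t) |
|---|---|---|
| 30 (stated requirement) | 89.8% | 88.8% |
| 28.8 (36 less 20%) | 88.5% | 87.4% |

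The loss due to the dropout step alone, from unrounded values, is 89.75 − 88.54 = 1.2 points by the normal approximation and 88.76 − 87.44 = 1.3 points by t-test.

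**The case against.** **The effect is slight.** About 1.3 percentage points of power and 1.2 expected patients per arm change no endpoint, analysis or conclusion. This stands, and it is why the point is minor.

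**The 20% might be meant as a top-up on the 30.** Six extra patients are 20% of 30. But the text speaks of patients dropping out, which is naturally a share of those recruited. On the top-up reading, the loss allowed for is 16.7% of recruits, and the sentence should say so.

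**Patients lost before month 12 may still contribute.** The plan compares scores with mixed models for repeated measures, and MDADI is collected at baseline and from month 3 onwards. Earlier scores then carry some information, so treating every dropout as wholly lost is conservative. This also stands. The gain cannot be quantified, because the article gives neither the correlation between visits nor the timing of dropout. It does not make 80% of 36 equal 30.

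**Stronger readings that the document does not support:**

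- *That 30 is itself an error.* The normal formula gives 30.26, and power at 30 is 89.8%, which is 90% to the nearest percent. This is ordinary rounding. A t-test would ask for slightly more (31.25), but the article does not say that a t-test was used.
- *That an arm will probably miss 30, so the design fails.* With 36 recruited and 80% retention, the binomial chance of keeping at least 30 in a given arm is 40%. With the matching 38 it is still only 66%. Such figures mostly reflect chance variation around an expected value, and planning to an expected value does not guarantee a count.
- *That the abstract is wrong.* It gives 36 and 108 with no dropout rate, evaluable number or power, so it contradicts nothing by itself.

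**Conclusion.** The sentence is wrong as written. A requirement of 30 per arm, 20% dropout and recruitment of 36 per arm cannot all hold; 36 leaves 28.8 expected per arm. The number consistent with the other two is 38 per arm, 114 in total.

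This is a minor correction. Power for one pairwise comparison is about 87.4% to 88.5% instead of the stated 90%, and part of that gap is rounding already present at 30. The power figures assume a two-sided 5% test of two arms and no use of partial follow-up from dropouts. They make no adjustment for comparing three arms or for the fixed centre effect that the plan intends to include. The shortfall from 30 to 28.8 needs none of these assumptions and follows from the plan's own figures.

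A reader might infer that the trial is materially underpowered because of this step. A loss of 1.2 to 1.3 points does not support that. Whether 30 per arm suits a three-arm comparison is a separate question, which this arithmetic does not settle.

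**What to change.** Either of two corrections makes the Statistical analysis section consistent.

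1. **Keep 36 per arm (108).** State that about 29 per arm are expected to be evaluable at 20% dropout, with power of roughly 87.4% (t-test) to 88.5% (normal approximation) for one unadjusted pairwise comparison. Alternatively, state that 36 allows for about 16.7% dropout. This changes wording only, needs no further patients, and leaves the abstract as it is.
2. **State 38 per arm (114)** as the number that gives 30 evaluable at 20% dropout. This costs six more patients, and the abstract must then be changed to match. It restores the stated 30 (38 × 0.8 = 30.4). By t-test, power at 30.4 is about 89.2%, so the 90% should be described as a normal-approximation figure after rounding.

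The first option is enough. Whichever is chosen, naming the test and its sidedness in the same sentence would let a reader reproduce the number.
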